## Abstract

**Introduction:**

Stigma and discrimination among healthcare workers can hinder diagnosis and the provision of appropriate care in dementia. This study is aimed at developing, delivering and evaluating the feasibility of a group antistigma intervention to improve knowledge, attitudes and behaviours in relation to people living with dementia among community health workers (CHWs).

**Methods and analysis:**

This will be a randomised controlled feasibility trial conducted with 150 CHWs from 14 primary care units (PCUs) in São Paulo, Brazil. PCUs will be randomly allocated (1:1) in two parallel groups—experimental group or control group. Participants from PCUs allocated to the experimental group will receive a 3-day group intervention involving audio-visual and printed materials as well as elements of social contact. The control group will keep their usual routine. Knowledge, attitude and intended behaviour stigma-based outcomes will be assessed at baseline and at follow-up (30 days after intervention) to both groups, with additional questions on feasibility for the experimental group at follow-up. Around 10–15 participants will take part in follow-up semistructured interviews to further explore feasibility. Quantitative analyses will follow an ‘intention to treat’ approach. Qualitative data will be analysed using content analysis.

**Ethics and dissemination:**

This study was approved by the National Commission for Ethics in Research in Brazil (n. 5.510.113). Every participant will sign a consent form. Results will be disseminated through academic journals and events related to dementia. The intervention materials will be made available online.

STRENGTHS AND LIMITATIONS OF THIS STUDYThis is the first study to develop, deliver and evaluate a controlled feasibility study of a group antistigma intervention to improve knowledge, attitudes and behaviours in relation to people living with dementia among community health workers in Brazil.This study will seek to involve all the community health workers of all the primary care units of a large urban city in São Paulo, Brazil.The study includes quantitative and qualitative components that will assess the feasibility of the intervention from different perspectives and will include a follow-up assessment, which will help us understand any potential long-term impact.As this will be a feasibility study, no conclusions can be drawn about the effectiveness of the intervention; however, we hope that the information collected will help build a robust future randomised controlled trial.

## Background

There are approximately 55.2 million people living with dementia worldwide and nearly 70% of this population live in low-income and middle-income countries (LMICs), such as Brazil.^1^ By 2050, this number is expected to increase to 139 million.^1^ Stigma and discrimination related to dementia are common, which is particularly important among healthcare workers, considering the detrimental impact on the lives of those living with the condition and their families, such as by hindering access to diagnosis and support.^2 3^ Combating the stigma related to dementia is a global health priority.^1^

Stigma occurs when a label associated with a negative stereotype is attributed to an individual characteristic, causing people with such characteristics to be seen as separate and of lower status compared with people without the characteristic.^4^ When stigma occurs, ‘power’ is exercised by stigmatisers to keep stigmatised groups ‘down’ or dominated/exploited; ‘within’, to maintain social norms; and ‘away’ by means of social exclusion.^5^ In dementia, stigmatisation occurs through negative stereotypes, related to cognitive decline can lead to depersonalisation and considering the person as unable to continue to live in and contribute to society.^6–9^ Although not every person living with dementia is an older person, older people living with dementia are likely to experience stigma related to dementia as well as from ageism and ableism, further impacting their rights and well-being.^10^

Several studies provide robust evidence on the negative impact that stigma and discrimination has on people living with mental disorders more broadly.^11–13^ Although there is a paucity of research on the impact of stigma on people living with dementia,^6^ the existing evidence shows that stigma can lead to negative feelings about one self, shame, symptom and diagnosis concealment, negative social interactions, reduced access to care networks and social participation and even suicide.^2 6 9 14–16^ A global survey on attitudes towards dementia among members of the public, people living with dementia, family carers and healthcare professionals from 155 countries showed that over 85% of respondents living with dementia had their opinion not taken seriously as well as between 35% and 57% (in high-income countries and LMICs, respectively) had been treated unfairly in intimate relationships. Moreover, 40% of the general public believed health professionals ignore people living with dementia; and 35% of carers reported hiding the diagnosis of dementia of a family member.^2^

Limited knowledge about dementia as well as widespread misbeliefs (eg, believing that dementia is a natural part of ageing) and negative attitudes (eg, considering people living with dementia are burdensome) may make health professionals less likely to detect dementia and provide adequate care to people affected by this condition.^3 9^ In over 75% of cases globally, diagnosis of dementia is either not made, or is made at a later stage, when the person living with the condition is no longer able to make decisions about their life and well-being independently.^3^ Structural forms of stigma—such as when systems, policies or services are designed in a way that discriminates directly or indirectly against people living with dementia^17^—also contributes to poor healthcare provision in dementia, by means of lack of investment in appropriate services and in training for health and social care providers, who continue to be unprepared to diagnose and to provide care and support for people living with dementia,^3^ further contributing to the experiences of stigma and discrimination experienced by these individuals. The current state of healthcare systems and providers can, therefore, be seen as a consequence as well as a source of stigma related to dementia.

A recent systematic review with 56 studies showed that most interventions to reduce mental health-related stigma in LMICs are effective.^18^ These were focused on stigma related to schizophrenia, suicide, depression, child and adolescent mental health, bipolar disorder, anorexia nervosa and post-traumatic stress disorder among healthcare workers, students or on more than one group. Around 75% found a significant positive effect for all main stigma outcomes and 25% found a small positive effect for some but not all stigma outcomes. Among the moderate or high-quality studies (n=38), 10 found a significant long-term positive effect on stigma outcomes.

The most common approach is education; however, a wide variety of methods—from creative arts-based approaches to those which emphasise empowering people with mental health conditions—can be successful, including social contact interventions.^18^ Currently, very little is known about interventions which reduce stigma related to dementia^19^ and research on knowledge and attitudes related to dementia in Latin American countries is scarce.^20 21^ There is an urgent need for further research on dementia-related stigma in different contexts and cultures.^1 6^

It has been estimated that 77% of people living with dementia in Brazil are not diagnosed.^22^ Prevalence estimates of people living with dementia vary from 5.1% to 19.0% among those aged 65 and over.^23^ Brazil still lacks well-funded and well-equipped health systems to meet the needs of the growing population of people living with dementia and their families. The country has a universal health system in which primary care units (PCUs) are the first point of access for people who experience any physical or mental health problem. In most regions, PCUs have community health workers (CHWs) who contribute to health promotion and disease prevention activities.^24^ Most CHWs live in the same communities where they work, being a valuable point of contact and an intersection between health services and their communities. Health systems with CHWs have the potential to help expand the delivery of mental healthcare and close the existing mental health gap in LMICs.^25^ However, the training activities offered to CHWs in Brazil is focused on the control of communicable diseases, maternal and child health and non-communicable physical diseases, such as diabetes and hypertension, with very little training dedicated to dementia. Providing CHWs with adequate knowledge on dementia, as well as on common stigmatising and discriminatory practices, and positive attitudes and behaviours towards people living with dementia may help increase the number of people living with dementia identified by the PCU as well as the quality of the healthcare and support provided to these individuals.

## Aim and objectives

The overarching aim is to design an antistigma intervention to reduce stigma and discrimination towards people living with dementia among CHWs in the city of São José dos Campos, Sao Paulo, Brazil and to pilot the intervention using a feasibility randomised controlled trial. The specific objectives are:

To develop a group-based intervention to improve knowledge about dementia as well as attitudes and behaviours towards people living with dementia.To test the intervention in a randomised controlled feasibility study and evaluate the acceptability and feasibility of performing such an intervention in a future randomised controlled trial.

## Methods and analysis

### Study design

A randomised controlled feasibility study will be conducted as part of a large multinational research programme (*Strenghtening Responses to Dementia in Developing Countries: STRiDE - www.stride-dementia.org*), which aims to contribute to the improvement of care systems, treatment and support for people living with dementia and their families in Brazil and other LMICs. An exploratory qualitative study was conducted previously involving semistructured interviews and focus groups with people living with dementia, family carers, healthcare workers and members of the public in three large cities in the state of Sao Paulo.^9 26^ The findings from the study helped inform the content and design of this intervention (table 1 and figure 1). This protocol (V.1; date: 4 May 2022) was prepared in line with the Standard Protocol Items: Recommendations for Interventional Trials checklist (online supplemental material I).^27 28^ The study protocol will be registered in the Brazilian National Registry of Clinical Trials (REBEC: https://ensaiosclinicos.gov.br/ or in ClinicalTrials.Gov https://clinicaltrials.gov/), which will include all items from the WHO Trial Registration Data Set (https://www.who.int/clinical-trials-registry-platform/network/who-data-set).

10.1136/bmjopen-2021-060033.supp1Supplementary data

**Table 1 T1:** Summary of the intervention components and activities

When		Why: what we want to achieve	What: topic covered	How: method or strategy
**Day 1:** Building knowledge and demystifying dementia: beginning the transformation process.	Session 1	To understand the general structure of the intervention and get to know one another, which will be important to build a non-judgmental space of trust among the individuals and for their spontaneous contribution to the activities. To get in touch with individual and shared beliefs and questions related to dementia, and to gain a better understanding of the condition and of the ‘individual behind the disease’.	What is dementia? What is not dementia? How people living with dementia are seen?	Before the session starts, we ask participants to individually write down their views on dementia and people living with dementia using directed questions. We provide an interactive presentation on knowledge and common beliefs related to dementia. Each participant reads their views and shares with the group voluntarily. The group reflects and discusses these based on the presentation delivered earlier.
	Session 2	To understand what dementia is, what dementia is not, and what treatment and care possibilities exist. To understand how dementia can affect people living with dementia and their families. To experience, through group dynamics, the impacts caused by prejudice, discrimination, and negative language on the lives of people living with dementia.	What is dementia? What is not dementia? Known and unknown, modifiable, and non-modifiable risk factors. Pharmacological and non-pharmacological interventions can help people who live with dementia and their carers to have quality of life. Management and control of dementia symptoms.	This will be a dynamic session in which we ask questions to the group in one slide, and provide feedback in the following slide, and so on. After, we will have the “secret box” dynamic: we will distribute individual boxes containing two photos of famous people and a mirror at the end. We ask participants to describe the characteristics of the two people and then to describe themselves. We try to identify differences in how they would describe ‘others’ and how they would describe ‘themselves’ to stimulate empathetic and non-judgemental approaches. We will hold a reflective and introductory debate on stigma, prejudice, discrimination, and use of language. We will promote reflection on how the participants felt when placing themselves in the ‘shoes’ of someone living with dementia.
**Day 2:** Breaking down labels and stereotypes and improving attitudes towards people living with dementia.	Session 1	To understand how thoughts, feelings, attitudes, and behaviours of other people affect people living with dementia. To understand that the consequences of stigma and discrimination that people living with dementia experience are as important as knowing the disease itself. To understand the power of language as a mechanism of prejudice and discrimination. To identify possible behaviours and inadequate attitudes towards dementia and people living with dementia among participants.	The importance of language, what is said and what is not said, in relation to people living with dementia, as well as common stigma and discrimination practices. Commonly used terms that reproduce stigma.	This will be a dynamic session in which we ask questions to the group in one slide, and provide feedback in the following slide, and so on. Re-read and hold a debate on the answers participants gave on the first day, prior to the intervention start and compare them with the views they have now about people living with dementia and their carers.
	Session 2	To understand that people living with dementia have desires, preferences, feelings, and aspirations. To sensitise participants about common negative behaviours, thoughts, and attitudes towards people living with dementia. To develop empathy for the everyday issues experienced by people living with dementia.	The heterogeneity of people living with dementia. Importance of looking at people who live with dementia in a holistic way, beyond the disease. Compassion, understanding, and empathy for everyday situations experienced by people living with dementia.	Show video narratives of people living with dementia Hand out two case vignettes to participants in which we depict two cases of people who develop dementia, and they have to read these in ‘first person’ as if the story described were theirs Hold a group discussion about how they felt in reading those experiences and about how they would have liked to be treated.
**Day 3:** Developing compassion and empathy and strengthening communication and behavioural skills.	Session 1	To explain and demonstrate positive verbal and non-verbal communication strategies. To apply these strategies in groups. To actively try to recognise possible transformations in their beliefs, attitudes, and behaviours related to people living with dementia compared with the beginning of the intervention.	Practical strategies for reflection on appropriate ways of caring for people living with dementia. Positive verbal and non-verbal communication strategies.	Content display using slides.
	Session 2	To identify inappropriate behaviours and attitudes in their own practices. To reflect on how to apply positive verbal and non-verbal communication strategies learnt in the previous session. To generate feedback on the six sessions held.	Importance of the CHWs work in combating the stigma of dementia.	Real-life-based stories about the daily life of people living with dementia are presented and discussed. Reflections and discussion of the theoretical contents discussed in the 3 days of intervention.

CHWs, community health workers.

**Figure 1 F1:**
[figure not shown]
Theory of change: stigma and discrimination related to dementia among community health workers.

### Participants and sampling

All CHWs in each of the 20 eligible PCUs located in São José dos Campos will be invited to take part. Individuals working as a CHWs for less than 3 months will be excluded. Each PCU has approximately from 8 to 12 CHWs, totalling 160 to 240 potential participants. A proportion (30%) of refusals to participate and dropouts are expected (eg, change in work schedules); therefore, we estimate to include approximately 14 PCUs involving around 150 participants in the trial.

#### Method of generating the allocation sequence

Randomisation and allocation will be conducted by blinded member of the research team at the PCU level using computer-generated random numbers. The PCUs whose managers agree to participate will be randomly allocated in two parallel groups—experimental group or control group—so that all CHWs of a given PCU who voluntarily accept to take part can be allocated in the same group forming a cluster and reducing the potential for contamination (eg, sharing knowledge learnt in the intervention between PCUs). The allocation will be made randomly at 1:1, so that there is the same number of PCUs in each group, offering as much as possible balanced participation among CHWs from PCUs located in the various geographical regions, proportional to the total number of PCUs of each region (20%: north, 20%: south, 20%: east, 20%: west, 20%: centre). The characteristics of participants (eg, age, gender, time working as CHW) will be compared between groups and controlled statistically if significant differences are observed.

Before informing the PCUs about the group to which their CHWs have been allocated, every CHWs wishing to participate will read and sign a consent form. Recruitment and enrolment will be conducted by a separate member of the team, who will be blinded to the allocation. Then, all participants will be invited to complete the baseline measures (t1). The experimental group will be informed about the dates and timings of the intervention and the control group will be told that they will be allocated to a waiting list. After the completion of the final assessments from both experimental group and control group (t2), the intervention will be offered to the control group.

**Figure 2 F2:**
[figure not shown]
Study flow.

### Assessment

#### Primary and secondary outcomes

The primary outcome will be the feasibility of the intervention, including the findings of a nested qualitative component. The secondary outcomes will be the stigma-related measures: knowledge, attitudes and intended behaviour. All the outcome measures are described as follows.

#### Baseline and poststudy assessment

Baseline (t0) and poststudy assessments (t2) will be the same for both experimental and control groups. Additional feasibility questions (closed and open questions) will be applied to the experimental group on the last day of the intervention as well as in t2, and 15–20 participants in the experimental group will be invited to participate in one-to-one semistructured interviews. Apart from the qualitative interviews, the written questions are all self-administered and will be completed on paper. Questionnaires will be distributed and collected by an assistant researcher who will be blinded to participant allocation. We hope that using anonymous self-administered questionnaires (identifiable only through participant code) will help mitigate any potential risk for social desirability bias. We will also highlight to participants that the questionnaires are not identifiable and that any answers they provide will not be linked to their names, and that they should be free to answer honestly to all the questions without any fear of being judged. The researchers applying the intervention will not have access to the participants’ responses until the end of data collection. It is expected that CHWs will take 10 min to 15 min to complete all the questions. Considering the acceptance of approximately 14 PCUs to participate in the study, it is estimated that the total period between t0 and t2 in all PCUs will be 90 days.

#### Sociodemographic and stigma-related outcomes

Sociodemographic questions will include age, gender, level of education, religion as well as information on previous training and experience with dementia (details in online supplemental material II). Stigma-related questions (dementia knowledge, attitudes and intended behaviour towards people living with dementia) were derived from the 2019 Global Stigma and Dementia Survey (WAR). The WAR questionnaire has been administered to more than 70 000 people worldwide, including healthcare professionals, members of the public, people living with dementia and their carers, through which process it has been translated to Brazilian Portuguese.^2^ The WAR questions were designed in Likert scale format and are concerned with the dementia knowledge, attitudes and anticipated behaviour towards people living with dementia. The questions were informed by existing validated stigma and discrimination scales^35 36^ and have been validated into a reduced number of items with high psychometric performance.^2 37^

10.1136/bmjopen-2021-060033.supp2Supplementary data

#### Feasibility assessment

First, a brief evaluation will be conducted on the last day of the intervention through discussion and notes will be taken by the researchers (eg, relevance, positive and negative aspects). Then, in t2, additional measures (objective and subjective) regarding the feasibility of the intervention will be applied, including a measure of satisfaction with the intervention^38^ and open questions (details in online supplemental material II). We will also collate information on recruitment rate and retention overall and per session, intervention completion rate, evaluation measures completion, appropriateness/acceptability and fidelity of the intervention. Provisional decision rules for what procedures to carry through to the full trial will include: retention of at least 70% completing at least two-thirds of the sessions, less than 15% missing on outcome measures and fidelity of at least 75% according to a fidelity checklist to be completed by a member of the research team in every session.^39–41^ Qualitative and quantitative findings will be collated and reported in a transparent, and the decision regarding whether the intervention is feasible or not will be taken (plus justified and reported) on discussion among the research team.

#### Nested qualitative component

Two participants from each PCU participating in the experimental group (n~14), including those who dropped out the study, will be invited to voluntarily participate in individual semistructured interviews to explore further aspects of feasibility and potential impact of the intervention (details in online supplemental material III). Interviews will take place on the same day of t2, after all the poststudy measures have been completed. The sample will be selected purposively, aiming to include a variety of sociodemographic characteristics, locations and background training on dementia. To reduce the potential selection bias based on the interpersonal experience of the researchers applying the intervention with the participants, another member of the team will make this selection based on the characteristics reported in the questionnaires, and another researcher will conduct the interview itself. The interviews will last a maximum of 60 min, will be voice recorded, and will be held in a private room at the PCUs where the CHWs work.

10.1136/bmjopen-2021-060033.supp3Supplementary data

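### Dropouts are meant to be interviewed, but the single t2-day, workplace slot and the selection criteria do not secure this; and the number invited conflicts (15–20 against about 14)

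*Protocol article*

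**What the plan says.** Primary and secondary outcomes makes the interviews part of the main result: "The primary outcome will be the feasibility of the intervention, including the findings of a nested qualitative component".

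Nested qualitative component states whom to invite: "Two participants from each PCU participating in the experimental group (n~14), including those who dropped out the study, will be invited". It then sets the timing: "Interviews will take place on the same day of t2, after all the poststudy measures have been completed". The place is a private room at the unit where the worker is employed. Selection is purposive, for variety in sociodemographic characteristics, location and previous dementia training. A team member makes the selection from what participants reported in the questionnaires.

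Two other places give an interview number:

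- Baseline and poststudy assessment: "15–20 participants in the experimental group will be invited to participate in one-to-one semistructured interviews".
- Abstract, Methods and analysis: "Around 10–15 participants will take part in follow-up semistructured interviews to further explore feasibility".

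**The concern.** People who leave are the best informants on why an intervention or a trial procedure did not work for them. The protocol recognises this by naming them as invitees. However, the one time and place it gives depend on the person being at the unit on the t2 day, and leavers are the group least certain to be there. The example it gives for refusals and dropouts, in Participants and sampling, is a change in work schedule, which is also a reason to miss a fixed day.

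The selection rule does not make up for this. Attendance and withdrawal are not among the named criteria, although Feasibility assessment says that retention will be recorded overall and per session. A team could satisfy every stated criterion and interview no leaver.

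The other sources of participant opinion do not fill the gap. The discussion on the last intervention day and the satisfaction and open questions at t2 also depend on people being present. The same section leaves the final feasibility decision to team discussion of the collated qualitative and quantitative findings. Interviews drawn mainly from completers could therefore make the intervention look more acceptable than it was.

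The second issue is simpler. Two sections each state how many people will be invited, and the figures differ.

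**Working it through.** **Number invited**

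Inputs:

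- About 14 primary care units (Participants and sampling).
- Allocation 1:1 by unit (Method of generating the allocation sequence).
- Two invitees per experimental unit (Nested qualitative component).

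The plan's own figure first: 14 ÷ 2 = 7 experimental units, and 7 × 2 = 14. This reproduces the stated n of about 14.

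Against the other figures:

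| Place | What is counted | Figure | Per experimental unit (÷ 7) | Contains 14? |
|---|---|---|---|---|
| Nested qualitative component | invited | about 14 | 2.0 | yes |
| Baseline and poststudy assessment | invited | 15–20 | 2.1 to 2.9 | no |
| Abstract | taking part | about 10–15 | not applicable | yes |

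The first two rows count the same thing and do not agree. The abstract counts people who take part. Ten interviews from 14 invitations is an uptake of 10/14 = 71%, and 10–15 interviews could also come from 15–20 invitations. The abstract therefore conflicts with neither.

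**Reaching people who dropped out**

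No formula applies here. The timing sentence can be read in two ways.

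1. Person by person: each interviewee must first have completed the t2 measures. Anyone who does not complete t2 is then shut out, against the stated intention to include dropouts.
2. By session: interviews follow the questionnaire session at that unit. A worker who stopped attending but is still employed there and present that day can then be interviewed.

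Under both readings, three kinds of leaver compare as follows:

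| Leaver | Reading 1 | Reading 2 |
|---|---|---|
| Left the sessions, still completes t2 | reachable | reachable |
| Left the study, at work on the t2 day, no t2 measures | not reachable | reachable |
| Absent on the t2 day, or no longer at the unit | not reachable | not reachable |

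The last row is the same under both readings, and that gap is the part of the point that stands. The middle row depends on the reading, so the sentence needs clarifying.

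**Size**

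The only loss figure is the 30% in Participants and sampling, which covers refusals and dropouts together. It matches the step from 20 eligible units to 14 (20 × 0.70 = 14). People who refuse never enter the experimental group, so the 30% is not a dropout rate among those who could be invited. No separate dropout rate is given, and the expected number of leavers among 14 invitees cannot be derived.

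**The case against.** The strongest reply is that the protocol expressly names dropouts as invitees, and that the timing sentence sets an order of events on the day and is not an eligibility condition. This stands. A reader might infer that the rule excludes all dropouts and delivers no interviews with them, but the documents do not support that. Interviews are held at the workplace, and a worker who has stopped taking part may still be there. Selection can use baseline questionnaires, which people who later leave will have completed. Someone who left the sessions may also still complete t2.

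A reader might also apply the 30% to the 14 places and conclude that about 4 belong to leavers (0.30 × 14 = 4.2). That figure fails because the 30% includes refusals, and because the sampling is purposive for variety and not proportionate.

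A third tempting reading is that the interview count is given in three incompatible ways. Only the two invited figures conflict. That conflict is also small (14 against a lower bound of 15) and rests on an approximate unit count: with 16 to 20 units, two per experimental unit would give 16 to 20 invitees. This softens the conflict but does not remove it, because the plan states 14 units and n of about 14.

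Finally, the numerical progression thresholds (at least 70% retention, under 15% missing, at least 75% fidelity) do not use the interviews. That is correct. The interviews still belong to the primary outcome and feed the team's overall decision.

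How many places go to leavers is detail that an article may leave to the full protocol. The time, the place and the selection criteria are not left open: the article states them, and as stated they serve its aim poorly.

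**Conclusion.** The point holds in two parts.

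First, the stated time and place give no route to leavers who are absent on the t2 day or have left the unit, and the named selection criteria do not ensure that any leaver is sampled. The qualitative part of the primary outcome may therefore lean towards completers. The direction, acceptability looking better than it was, is plausible but not proven. The size is unknown, because the document gives no dropout rate separate from refusals. The conclusion assumes that the article's description is followed as written, with no additional route in the full protocol.

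Second, the number invited is inconsistent at the plan's own 14 units: 15–20 in one section and 14 in another. The discrepancy is small and affects no stated threshold, but one figure has to be corrected.

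**What to change.** - In Nested qualitative component, allow people who do not attend t2 to be interviewed at another time or by phone. Make clear that completing the t2 measures is not a condition for an interview.
- Add session attendance or withdrawal status to the purposive criteria, using the retention records already planned. The number of places for leavers can be left to the team.
- State one invited number in Baseline and poststudy assessment and in Nested qualitative component. At the planned 14 units, the two-per-unit rule gives 2 × 7 = 14. The abstract's figure can stay, since it counts people taking part.

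The cost is a few rescheduled interviews and a way to obtain the separate interview consent away from the visit. Some leavers will decline, so the change reduces the lean towards completers and does not remove it. The total number of interviews need not rise. Ethics and dissemination says that the study stops until important modifications are approved, so this is best settled before the start.
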